#### Early completers

We will allow “early completion” when symptoms resolve before the nine sessions are finished. A participant will be considered an early completer of treatment when his or her score on the PTSD Symptoms Scale—Self Report (PSS-SR) is lower than 10 on two consecutive occasions, and if the SUD scores from all situations that are part of the case conceptualization are reduced to zero. If this happens, therapy can be stopped early.

### Measures

#### Demographic data

Demographic data collected will include age, gender, ethnicity, mental health diagnoses, legal status, and index offence (the offence/s for which they are currently detained) details, including date and type, relationship of the victim, and intoxication at the time of the event.

#### Outcome measures

A range of primary, secondary, and tertiary outcome measures (all outlined in the following, see Fig. 2) will be administered at baseline (T0), post treatment (T1, at 10 weeks), and at 6-month follow-up (T2). After T2, participants will be invited to engage in a semi-structured interview (see Subjective experiences of EMDR: qualitative data collection) to gather data on their subjective experience of PTSD and EMDR.

**Fig. 2 Fig2:**
[figure not shown]
Standard Protocol Items: Recommendations for Interventional Trials (SPIRIT) figure. AEQ, Adverse Events Questionnaire; BDI-II, Beck Depression Inventory—second edition; CAPS, Clinician Administered PTSD Scale; EMDR, eye movement desensitization and reprocessing; PSS-SR, Posttraumatic Stress Disorder Symptom Scale—Self-Report; PTCI, Posttraumatic Cognitions Inventory; PSYRATS, Psychotic Symptom Rating Scales; RSES, Rosenberg Self-Esteem Scale; SFS, Social Functioning Scale; TAAS, Treatment Acceptability/Adherence Scale; TSI-2, Trauma Symptom Inventory—second edition; WHODAS, World Health Organization Disability Assessment Scale

T2 is the starting point for treatment for the waiting list group. For participants in the EMDR group, additional treatment-related assessments take place within sessions (see later).

#### Primary outcome measurements: PTSD symptoms, adverse events, and treatment acceptability

There are two primary outcome measures pertaining to PTSD symptoms, two regarding treatment safety, and one measure of the acceptability of EMDR treatment. The first primary outcome measure is the CAPS, which is a 30-item structured interview that assesses DSM-5 PTSD symptoms [37]. The CAPS will be used to assess the presence or absence of PTSD diagnosis and the frequency and intensity of the clinician-rated PTSD symptoms.

**Table 1 Tab1:** Secondary outcome measures

Secondary outcome	Measurement instrument^a^	T0	T1	T2
Posttraumatic cognitions	PTCI (s)	X	X	X
Self-disturbance	TSI-2 Factor 1 (s)	X	X	X
Posttraumatic stress	TSI-2 Factor 2 (s)	X	X	X
Externalization	TSI-2 Factor 3 (s)	X	X	X
Somatization	TSI-2 Factor 4 (s)	X	X	X
Depression	BDI-II (s)	X	X	X
Psychosis	PSYRATS (i)	X	X	X
Overall functioning	WHODAS 2.0 (i)	X	X	X
Social functioning	Social Functioning Scale (i)	X	X	X
Self-esteem	RSES (s)	X	X	X

^a^ (i) = measurement interview, (s) = self-report

BDI-II, Beck Depression Inventory—second edition; PTCI, Posttraumatic Cognitions Inventory; PSYRATS, Psychotic Symptom Rating Scales; RSES, Rosenberg Self-Esteem Scale; T0, baseline; T1, post treatment; T2, 6-month follow-up; TSI-2, Trauma Symptom Inventory—second edition; WHODAS, World Health Organization Disability Assessment Scale

**Table 2 Tab2:** Items from the World Health Organization Trial Registration Data Set

Data category	Information
Primary registry and trial identifying number	Australia and New Zealand Clinical Trials Network, registration number ACTRN12618000683235 (registered prospectively)
Date of registration in primary registry	26 April 2018
Sponsor	University of Otago Contact details: Office of Research and Enterprise, Otago University, [name]. Tel. [name]
Contact for public/scientific queries	[contact]
Public title	Eye movement desensitization and reprocessing (EMDR) therapy for posttraumatic stress disorder in adults with serious mental illness within forensic and rehabilitation services: a study protocol for a randomized controlled trial
Scientific title	Eye movement desensitization and reprocessing (EMDR) therapy for posttraumatic stress disorder in adults with serious mental illness within forensic and rehabilitation services: a study protocol for a randomized controlled trial
Countries of recruitment	New Zealand
Health condition(s) or problem(s) studied	PTSD in people receiving care from forensic mental health services
Intervention(s)	EMDR therapy
Key inclusion and exclusion criteria	Inclusion criteria: aged 18–65 years; a lifetime history of a psychotic disorder or a mood disorder with psychotic features as diagnosed according to ICD-10 or DSM-5 criteria; meeting diagnostic criteria for PTSD (Clinician Administered PTSD Scale (CAPS)); current patient of the forensic and rehabilitation mental health services; competent to provide informed consent; likely to remain in the area for the 6-month trial duration (i.e., if a prisoner, release date at least 6 months away; if a patient within a forensic mental health service, their anticipated discharge is at least 6 months away) Exclusion criteria: high suicidality, operationalized as the combination of having a high suicidality score on the Mini International Neuropsychiatric Interview (MINI-plus) or with a suicide attempt within the past 6 months; mental state considered by the treating psychiatrist as too unstable to participate in the trial (participants may be experiencing chronic low-grade symptoms, but cannot be acutely psychotic); insufficient competence in the English language to understand, provide informed consent, and participate in therapy and data collection
Study type	Single-blind, randomized controlled trial
Date of first enrolment	25 May 2018
Target sample size	46
Recruitment status	Currently recruiting
Primary outcome(s)	Change in PTSD symptoms (measured by the CAPS and PSS-SR), treatment safety (measured by the adverse event questionnaire), and acceptability of the EMDR treatment (measured by the TAAS and by qualitative participant feedback)
Key secondary outcomes	Posttraumatic cognitions (PTCI), self-disturbance (TSI-2 Factor 1), posttraumatic stress (TSI-2 Factor 2), externalization (TSI-2 Factor 3), somatization (TSI-2 Factor 4), depression (BDI-II), psychosis (PSYRATS), overall functioning (WHODAS 2.0), social functioning (Social Functioning scale), self-esteem (RSES)

BDI-II, Beck Depression Inventory—second edition; DSM-5, *Diagnostic and Statistical Manual of Mental Disorders*, fifth edition; EMDR, eye movement desensitization and reprocessing; ICD-10, International Classification of Diseases, 10th edition; PSS-SR, Posttraumatic Stress Disorder Symptom Scale—Self-Report; PTCI, Posttraumatic Cognitions Inventory; PSYRATS, Psychotic Symptom Rating Scales; PTSD, posttraumatic stress disorder; RSES, Rosenberg Self-Esteem Scale, TAAS, Treatment Acceptability/Adherence Scale; TSI-2, Trauma Symptom Inventory—second edition; WHODAS, World Health Organization Disability Assessment Scale

We will consider the CAPS to provide a diagnosis of PTSD if the person scores positively for all of the following conditions [11]:
At least one of the Criterion B symptoms (“re-experiencing” symptoms, relating to diagnostic items 1–5 in the CAPS)At least one of the Criterion C symptoms (“avoidance” symptoms, relating to diagnostic items 6–7 in the CAPS)At least two of the Criterion D symptoms (“negative alterations in cognition and mood”, relating to diagnostic items 8–14 in the CAPS)At least two of the Criterion E symptoms (“hyperarousal” symptoms, relating to diagnostic items 15–20 in the CAPS) OR at least one Criterion E symptom for the subset of participants taking therapeutic doses of marked or moderately sedating antipsychotics (specifically, clozapine ≥ 250 mg/day, olanzapine ≥ 15 mg/day, or quetiapine ≥ 300 mg/day [28])ANDCriterion F is met (disturbance has lasted 1 month)Criterion G is met (disturbance causes either clinically significant distress or functional impairment)

The CAPS is considered the gold standard to diagnose posttraumatic stress disorder and to establish its severity. A review of the empirical literature on psychometric properties of the CAPS [32] found that the CAPS has excellent reliability (> 0.90), yielding consistent scores across items, raters, and testing occasions. There is also strong evidence of validity with excellent (> 0.90) convergent and discriminant validity, diagnostic utility, and sensitivity to clinical change.

Secondly, the Posttraumatic Stress Disorder Symptom Scale—Self-Report (PSS-SR) [38] will be administered to assess self-reported severity of PTSD symptoms [39]. The PSS-SR consists of 17 items corresponding to the 17 diagnostic DSM-IV-TR criteria of PTSD which are rated on a 3-point Likert scale, where 0 = *not at all*, 1 = *a little* bit, 2 = *somewhat*, and 3 = *very much*. This yields a total score measuring symptom severity (range 0–51), as well as separate severity scores for re-experiencing (range 0–15), avoidance (range 0–21), and arousal (range 0–15). The PSS-SR will also be administered at T0, T1, and T2, as well as before each treatment session, to assess changes in the PTSD symptoms during treatment. The PSS-SR has revealed satisfactory internal consistency (Cronbach’s α = 0.91), high test–retest reliability (*r* = 0.74), and good concurrent validity (sensitivity = 62%, positive predictive power = 100%, negative predictive power = 82% [38, 40]).

Two primary outcome measures pertain to adverse events. The Adverse Events Questionnaire (AEQ), which we have designed using similar questions to Van den Berg et al. [16], is a checklist that will help establish treatment safety. In 10 questions, the patient is asked to report any experiences they have had over the last 2 months of self-harm, suicide attempt, deliberately hurting another person, excessive use of alcohol, excessive use of drugs, having needed help because of a crisis, moving back to a higher level of security within the services, or any reoffending.

The Adverse Events Session Rating scale will also be used to assess adverse events in the participant before and after treatment sessions (sessions two and three), for example, being suicidal and hearing voices. Participants will respond on a 10-point visual analog scale (from “*no, not at all*” to “*yes, very much*”) to the questions.

Finally, acceptability of treatment will be assessed using the Treatment Acceptability/Adherence Scale (TAAS) [41]. The TAAS was developed to assess the acceptability of cognitive behavioral therapy (CBT) treatments for anxiety disorders, following the observation that despite such therapies having a strong evidence base, dropout rates may be high. It was selected for the trial given the view that EMDR can be seen as a form of CBT [42], the historical placement of PTSD among anxiety disorders within psychiatric classification schemes [31], and research showing the TAAS to have sound psychometric properties [41].

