## Study aims

### Primary aim

In a sample of people receiving forensic and rehabilitation mental health care, we aim to examine: the efficacy of EMDR versus the waiting list for treating PTSD symptomology; and the safety and acceptability of EMDR versus the waiting list as indicated by adverse events.

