### Quantitative data analysis

Data analyses will be performed by a biostatistician blinded to treatment allocation using intention-to-treat and per-protocol analyses. The per-protocol analysis group refers to those participants who completed the treatment as originally allocated. We have defined this as participants who undergo at least six of the maximum nine total number of EMDR treatment sessions or who fulfill the criteria for early completion.

Baseline differences in demographic and clinical characteristics between the EMDR and control group will be analyzed using chi-squared tests, *t* tests, and analysis of variance. Descriptive statistics will provide data summaries. Continuous variables will be analyzed on an intention-to-treat basis with linear mixed models. For the PSYRATS data, which is usually not normally distributed because of a disproportionate number of zero scores, differences will be analyzed using the Wilcoxon signed-rank test and the Mann–Whitney *U* test.

Baseline scores will be included as covariates, time as a categorical variable, and treatment condition as a fixed effect. The intercept will be treated as a random effect. Dichotomous outcomes will be analyzed with logistic generalized estimating equation analyses with exchangeable correlation structure.

Effects will be calculated for post treatment and 6-month follow-up using interaction effects. Analyses of completers and intent-to-treat analyses with the last observation carried forward (with missing data on loss of diagnosis conservatively replaced with a negative value, i.e., no loss of diagnosis) will be performed to test the robustness of the findings.

The number needed to treat will be calculated to determine the number of participants who needed to be treated to make one more patient lose the PTSD diagnosis or achieve full remission compared with the control condition.

All tests will be two-sided and *p* < 0.05 will be considered statistically significant. We will use multiple imputations for missing data.

A biostatistician is part of the research team.

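### CAPS and PSS-SR are both primary for efficacy at two time points, each tested at an unadjusted two-sided 0.05, while the sample size rests on one post-treatment CAPS comparison

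*Protocol article*

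**What the plan says.** The section on primary outcome measurements states: "There are two primary outcome measures pertaining to PTSD symptoms, two regarding treatment safety, and one measure of the acceptability of EMDR treatment". The symptom measures are the CAPS, rated by a blinded assessor, and the PSS-SR, completed by the participant. The safety measures are the AEQ and the Adverse Events Session Rating scale, and the acceptability measure is the TAAS. CAPS is described first, but no rule says which result decides efficacy. CAPS also has two uses: "The CAPS will be used to assess the presence or absence of PTSD diagnosis and the frequency and intensity of the clinician-rated PTSD symptoms".

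Under Quantitative data analysis, neither time point is singled out: "Effects will be calculated for post treatment and 6-month follow-up using interaction effects". The same section sets one threshold for everything: "All tests will be two-sided and *p* < 0.05 will be considered statistically significant".

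Sample size calculations uses CAPS only: a difference of 16 points and an SD of 16, two-sided alpha 0.05, power 0.8, giving 15 per arm, or 23 per arm after 30% attrition. The 16 points come from post-treatment scores in an earlier trial.

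The list of primary outcomes differs by place. The Abstract gives clinician- and participant-rated PTSD symptoms and adverse events. The outcome section gives the five measures above. Table 2 gives CAPS, PSS-SR, the adverse event questionnaire and "acceptability of the EMDR treatment (measured by the TAAS and by qualitative participant feedback"; the Session Rating scale is absent and qualitative feedback is added.

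**The concern.** The design supports one test at 5%, but the decision rule allows several. A trial with a null blinded CAPS result and a PSS-SR result of p = 0.04 at either visit could be reported as positive on a primary outcome without departing from the protocol.

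The PSS-SR is the weaker of the two routes. Participants know their allocation, so self-report is open to expectation. The scale is also completed before each treatment session. The waiting list has no sessions until T2, so exposure to this primary measure differs between arms during the comparison.

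A separate difficulty is that the Session Rating scale is given around sessions two and three. During the randomized comparison those sessions exist only in the EMDR arm, so a listed primary outcome yields no between-arm estimate.

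Finally, three differing lists leave room to choose at reporting which set was primary.

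**Working it through.** **1. The plan's own sample size.** Inputs from Sample size calculations: difference 16, SD 16, two-sided alpha 0.05, power 0.80, 1:1 allocation.

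- Normal approximation: n per arm = 2 × (1.960 + 0.842)² × (16/16)² = 15.7, so 16. The exact t calculation gives 17.
- The stated 15 is close to both; I do not treat the gap as an error.
- With 30% attrition, 16/0.7 = 22.9, so 23 per arm, as stated.

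The recruited number therefore reproduces for one CAPS comparison at alpha 0.05.

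**2. Counting the efficacy tests.** Two primary symptom measures × two time points (T1, T2) = 4 between-arm tests. This leaves out CAPS diagnosis, which is also analysed, so it is a low count.

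**3. Chance of any false two-sided rejection, no true effect.**

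- Independent tests: 1 − 0.95⁴ = 1 − 0.8145 = 18.5%.
- Correlated tests: the documents give no correlations, so I assume values. I simulated four normal test statistics, with the cross-measure, cross-time correlation set to the product of the other two.

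| Between measures | Between times | Any two-sided rejection | Any rejection favouring EMDR |
|---|---|---|---|
| 0 (exact) | 0 (exact) | 18.5% | 9.6% |
| 0.5 | 0.5 | 16.2% | 8.1% |
| 0.7 | 0.6 | 14.4% | 7.2% |
| 0.8 | 0.7 | 12.7% | 6.4% |

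**4. Chance of a false claim in favour of EMDR.** A two-sided 5% test gives 2.5% in the favourable direction. For four independent tests, 1 − 0.975⁴ = 9.6%. The correlated values are in the last column. The reference for a single test is 2.5%.

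**5. What simple alpha splitting would cost.** Bonferroni over four tests uses alpha 0.0125. The normal approximation gives 22.3, so 23 evaluable per arm, and 23/0.7 = 32.9, so 33 recruited per arm against 23 planned (exact t: 24 and 35). With 16 evaluable per arm, power on CAPS at alpha 0.0125 is 57% by exact t. Fixed-order testing avoids this cost, because each test in the sequence uses the full 0.05.

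**6. Measures without a comparator.** The Session Rating scale belongs to sessions two and three, and T2 is when waiting-list participants start treatment (text under Fig. 2). Before T2 the scale therefore exists in one arm. For the TAAS, the article says it measures acceptability of EMDR, but it also says the primary measures are given at T0, T1 and T2 without restricting any by arm.

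**The case against.** Several points on the other side deserve weight.

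- A reader might infer ten tests (five measures × two visits), with an error rate of 1 − 0.95¹⁰ = 40.1%. The text does not support that. A one-arm measure gives no between-arm test, and the Session Rating scale is not a T1 or T2 measure. Four is the supportable count for efficacy.
- A reader might take 18.5% as the chance of a false claim that EMDR works. It is the chance of a rejection in either direction; the favourable direction is 9.6% at most for four tests with non-negative correlation.
- A reader might infer that the TAAS is given only in the EMDR arm. No sentence says so, and the schedule figure is not shown. It is simply unstated.
- The primary aim is worded as "the safety and acceptability of EMDR versus the waiting list as indicated by adverse events". The AEQ can serve that aim, so the one-arm measure does not defeat it.
- A reader might fear that a non-significant AEQ comparison will be presented as proof of safety. Nothing in the article says it will be.
- The choice of T1 is not forced. The difference comes from post-treatment data, but the 30% attrition is justified partly by losses by 6 months. The choice belongs to the sponsor.
- The outcomes are registered, recruitment began in May 2018, and early efficacy data are foreseen after 2 × 8 participants, with interim analyses going to a committee that includes the principal investigator. A change of hierarchy needs disclosure for that reason. It does not defeat the fix: all measures are still collected and reported, and only the order of testing is set.
- The differences between the three lists are largely editorial, the Abstract being a summary.

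The absence of an adjustment could often be left to an analysis plan. Here the protocol itself fixes the threshold for all tests, so the point stands.

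**Conclusion.** The point holds for efficacy. There are four co-equal primary tests at an unadjusted 0.05, and a sample size that covers one of them. The chance of at least one false rejection rises from 5% to 18.5% if the tests are independent, or about 13% to 16% under the assumed correlations. The chance of a false result favouring EMDR rises from 2.5% to 9.6%, or about 6% to 8%. These figures assume no true effect on either measure at either time, and the correlated values rest on my assumed correlations of 0.5 to 0.8.

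It also holds that the Session Rating scale has no comparator before T2 and that the primary lists disagree. The text establishes neither a TAAS restricted to one arm nor an intention to read a null AEQ result as safety. This should be changed; it does not undermine the design.

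**What to change.** Before unblinding:

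1. Name CAPS total severity at one time point as the single primary efficacy endpoint at two-sided 0.05. T1 matches the post-treatment difference used for sizing.
2. Test the other CAPS time point, then PSS-SR at T1, then PSS-SR at T2, in that fixed order, stopping formal claims at the first non-significant result.
3. Report the Session Rating scale descriptively within the EMDR arm, and state in which arms the TAAS is given.
4. Report the AEQ by arm as risk differences with 95% confidence intervals.
5. Use one primary list in the Abstract, the outcome section and Table 2.

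The cost is wording in the protocol and analysis plan, plus an update of the registered hierarchy that discloses the date of the change and what outcome data had been seen by then. Alpha stays at 0.05 and 23 per arm is unchanged. The downside is that a PSS-SR result alone can no longer carry the efficacy claim.

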### Withdrawal of participants from treatment

Participants may withdraw from the study for any reason or at any time. The investigators may also withdraw participants from the study if there are concerns about their safety and/or if they are unwilling or unable to comply with study procedures. The criteria for discontinuing EMDR treatment include the following: the participant does not attend for more than three consecutive treatments or for more than four treatments in total; serious adverse events (defined in the next section); participant request; and Data Monitoring Committee recommendation (described in the next section). As already described, we will analyze participants using intention-to-treat methods.

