### Trial monitoring and oversight

The risks of the study are thought to be low based on previous research, which has found EMDR to be safe, effective, and well tolerated in people with serious mental illness. However, the population is vulnerable so there are a number of safeguards in place. A Data Monitoring Committee (DMC) has been set up as an advisory body responsible for monitoring emerging safety and efficacy data, reviewing trial conduct and making recommendations. The DMC is independent of the study organizers and funders. Its membership is multidisciplinary and comprises the Clinical Director (Chair) and Operations Manager from the Central Regional Forensic and Rehabilitation Service, a senior psychologist not related to the study, and the principal investigator. During the recruitment period, interim analyses will be supplied in strict confidence to the DMC, together with any analyses the DMC may request.

The base rate of serious events in this population is much higher than in the general population, and it may be difficult to establish whether such events are related or unrelated to therapy. All serious adverse outcomes will be reported immediately to the DMC. We have predetermined that any serious event such as a serious deliberate self-harm attempt (requiring medical attention), an assault on another person (requiring medical attention), or a return to an environment of high security will be a reason for the participant being withdrawn from the study. Any other significant adverse effects will be discussed on a case-by-case basis. The DMC and research team will formally review the feasibility and safety of the study after data have been collected on 10 participants, before further participants are recruited.

The terms of reference of the DMC are available on request from the principal investigator.

In the unlikely event that someone is harmed in the course of the trial, they would be eligible under New Zealand law to apply for compensation from the Accident Compensation Corporation. This is explained in the informed consent process.

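### The only primary safety measure that compares the arms is patient self-report, and the serious events that trigger withdrawal and go to the DMC are not stated to enter it

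*Protocol article*

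**What the plan says.** All references are to the protocol article.

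- **Aim.** Study aims makes the safety of EMDR against the waiting list, judged by adverse events, part of the primary aim.
- **Instruments.** The section on primary outcome measurements states: "Two primary outcome measures pertain to adverse events". The first is the AEQ, a ten-question checklist in which "the patient is asked to report any experiences they have had over the last 2 months of self-harm, suicide attempt, deliberately hurting another person". Further items cover alcohol, drugs and crisis help, and the list ends with "moving back to a higher level of security within the services, or any reoffending". The second is a session rating scale, also answered by the participant, used "before and after treatment sessions (sessions two and three").
- **Table 2.** The primary outcome entry reads "treatment safety (measured by the adverse event questionnaire") and names no other safety source.
- **Serious events.** Under Trial monitoring and oversight, self-harm needing medical attention, an assault needing medical attention, or a return to high security "will be a reason for the participant being withdrawn from the study". The same section has all serious outcomes reported to the DMC at once.
- **Stopping treatment.** Withdrawal of participants from treatment says "The criteria for discontinuing EMDR treatment include the following", and serious adverse events are on that list.
- **Follow-up.** The retention text that closes the section on secondary outcome measurements plans T1 and T2 where possible for people who stop treatment. It also commits the investigators to following everyone enrolled to the end of the study as far as they reasonably can.

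**The concern.** A primary safety comparison should count the gravest events most reliably. Here it rests on what participants choose to disclose. Several items (hurting someone, reoffending, drug use) can carry legal or placement consequences for prisoners and secure patients, so incomplete disclosure is a reasonable inference, although the article gives no data on it.

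The withdrawal rule adds a second route to loss. If withdrawal from the study ends assessment, the participant gives no AEQ covering the event that caused the withdrawal. The trial would know of the event through the DMC report, while its primary safety outcome could omit it.

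At stake is the reading of a null result. If serious events are missing from the outcome, similar AEQ counts in the two arms would be weak evidence that EMDR is safe in this population.

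**Working it through.** The plan gives no figure for the safety outcome. Its only design calculation (15 per arm, 23 per arm after 30% dropout) concerns the CAPS and has no bearing here. The check is mainly a comparison of passages.

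**Step 1: which measure can compare the arms?** The session rating scale needs EMDR sessions two and three. The waiting list has none before T2, since the note under Fig. 2 says "T2 is the starting point for treatment for the waiting list group". That leaves the AEQ, which agrees with Table 2.

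**Step 2: do the withdrawal events overlap the AEQ?**

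| Event named under Trial monitoring and oversight | Related AEQ item |
|---|---|
| Self-harm needing medical attention | Self-harm, suicide attempt |
| Assault needing medical attention | Deliberately hurting another person |
| Return to high security | Move back to higher security |

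All three overlap. Drug use, alcohol use, reoffending, and self-harm or assault that needs no medical attention are not named there. The list is given by way of example, and other significant effects are handled case by case.

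**Step 3: is an AEQ collected after such an event?** One section withdraws the person from the study. Another treats serious adverse events as a reason to stop EMDR. The retention text promises follow-up to the end. Read together, they do not settle the question.

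**Step 4: do DMC reports enter the outcome?** Neither Table 2, nor the section on primary outcomes, nor Quantitative data analysis says so. The planned imputation and last-observation-carried-forward analyses are not described as using them either.

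**Step 5: can a direction between arms be derived?** Let the observed risk be p × s × (1 − q × l), where p is the true risk, s the share disclosed, q the share of events that trigger withdrawal, and l the share of those people never assessed afterwards. Every value below is assumed, because the documents give none: p = 0.20 in both arms, q = 0.40.

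| Scenario | EMDR | Waiting list | Difference (EMDR − waiting list) |
|---|---|---|---|
| s = 0.7 and l = 0.5 in both arms | 0.20 × 0.7 × 0.80 = 0.112 | 0.112 | 0 |
| s = 0.8 EMDR, 0.6 waiting list; l = 0.5 | 0.20 × 0.8 × 0.80 = 0.128 | 0.20 × 0.6 × 0.80 = 0.096 | +0.032 |
| s = 0.6 EMDR, 0.8 waiting list; l = 0.5 | 0.096 | 0.128 | −0.032 |
| s = 0.7; l = 0.8 EMDR, 0.3 waiting list | 0.20 × 0.7 × 0.68 = 0.095 | 0.20 × 0.7 × 0.88 = 0.123 | −0.028 |
| s = 0.8 EMDR, 0.6 waiting list; l = 0.8 EMDR, 0.3 waiting list | 0.20 × 0.8 × 0.68 = 0.109 | 0.20 × 0.6 × 0.88 = 0.106 | +0.003 |

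With p = 0.40 every difference doubles. The sign follows the assumptions put in, so no direction can be derived.

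**Step 6: what does one missed person cost?** With 23 per arm, 1/23 = 4.3 percentage points on that arm's event proportion.

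**The case against.** **Serious events are not lost to the trial.** They go to the DMC, and the retention text plans continued follow-up. This stands, and it limits the point: the events may be missing from the primary safety outcome, not from the trial's knowledge. It also makes the repair cheap.

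**Disclosure may matter little for the gravest events.** The host service would normally learn of an injury needing treatment or a security move whatever the questionnaire says. That is fair. It supports using that knowledge in the outcome, which the text does not do.

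**A condensed article may leave such detail to the full protocol.** This holds for operational checks of answers against records. It does not cover the data source of a primary outcome, which Table 2 states, or three statements on withdrawal and follow-up that do not fit together.

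**Stronger readings that the documents do not support.**

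- A reader might infer that the waiting list under-reports more, because its EMDR starts only at T2 and disclosure could put that at risk. No passage says that an AEQ answer or study withdrawal forfeits later EMDR. EMDR participants also have treatment to lose while in it, and closer contact could detect and withdraw more of them. In addition, heavier under-reporting on the waiting list would make EMDR look worse, so it would not falsely reassure.
- A reader might infer that any adverse answer removes the person. The rule concerns serious events.
- A reader might conclude that records should replace self-report altogether. Participants come from inpatient, custodial and community settings, and the service covers five prisons, so full extraction is not trivial. Recorded events can also be subject to unequal detection.

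**Conclusion.** The point holds in limited form and should be fixed. Followed as written, the primary safety comparison rests on the AEQ alone and can miss serious events that the trial already captures by another route.

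Two links are inference. One is that some participants will not disclose. The other is that withdrawal from the study may end AEQ collection, which the article leaves unsettled. The overlap between withdrawal events and AEQ items, and the absence of any stated link from DMC reports to the outcome, are read directly from the text.

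The number of events missed cannot be estimated. The article calls the base rate of serious events much higher than in the general population but gives no figure. Whether the loss differs by arm, and in which direction, cannot be determined either; the scenarios above only show that either sign is possible. What can be said is that each affected participant missed moves an arm of 23 by 4.3 percentage points, so a handful of omissions could change the safety conclusion.

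**What to change.** 1. **Redefine the outcome.** Make the primary safety outcome the AEQ plus the serious-event reports already collected for the DMC, supplemented by service-recorded security moves where these are accessible.
2. **Use one rule for both arms.** Count these events for every randomised participant from T0 to T2, by the same definition in each arm, with classification blind to allocation. Continue the count after withdrawal where consent allows.
3. **Keep self-report for what no record shows.** Report AEQ answers on unrecorded behaviour, such as excess alcohol or drug use and untreated self-harm, separately from the serious-event count.
4. **Reconcile the passages.** Trial monitoring and oversight (withdrawn from the study), Withdrawal of participants from treatment (EMDR discontinued) and the retention text (followed to the end) must agree on whether safety data are still collected after such an event. This is a question about data collection; when treatment should stop is for the investigators.
5. **Show results by source.** Clinician-sourced reports may pick up more events in the EMDR arm because contact is closer. Presenting AEQ and reported events side by side lets readers see this.

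The cost is modest: some linking and blinded classification of reports for 46 participants, and possibly consent wording for safety data after withdrawal. Access to security-move records will vary by setting, which is why they are a supplement.
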